#### **8.2.2.2 HPV Test and Genotyping (Anyplex HPV28)**

The Anyplex II HPV28 (Seegene, Inc) will be used for detection and genotyping of HPV DNA in cervical, anal, urine, vulvar and oral samples from the study subjects. The purpose of the test is to distinguish reduction of infectivity due to 9vHPV vaccination from spontaneous clearance of the HPV infection.

Anyplex II HPV28 is a semi-quantitative method based on real-time PCR able to detect and identify 19 high risk-HPV types (16, 18, 26, 31, 33, 35, 39, 45, 51, 52, 53, 56, 58, 59, 66, 68, 69, 73, 82) and 9 lower risk-HPV types (6, 11, 40, 42, 43, 44, 54, 61, 70) with high sensitivity and specificity.

Samples will be subjected to DNA isolation prior to Anyplex II HPV28 assays with automated Maxwell® RSC Tissue DNA Kit (Promega) according to manufacturer instructions. The genotyping assay comprises multiplex real-time PCR reactions with type-specific primers and probes for the detection of all mentioned HPV types. The type-specific probes are each labelled with a different fluorescent label, and the fluorescent emission is captured by the CFX96 thermal cycler (BioRad). Fluorescent signal intensity correlates with the abundance of the target DNA and a Ct value is assigned according to the cycle in which fluorescent signal exceeds a threshold. Positivity for a given HPV type will be considered when Ct<35. Human beta-globin will also be analyzed as internal control of cellularity.

The Anyplex II HPV28 is a validated method and currently in use for clinical diagnosis.

#### **8.2.2.3 Anti-HPV L1 ab Detection: Competitive Luminex Immunoassay (cLIA) and Immunoglobulin-G Luminex Immunoassay (IgG LIA)**

The 9-valent HPV cLIA will be used as a primary method to evaluate antibodies specific for HPV vaccine-covered types (6, 11, 16, 18, 31, 33, 45, 52, and 58) in serum samples from study's subjects of RIFT-HPV Cohort 1. Antibodies against HPV types 16 and 18 will be also evaluated using ELISA (section 8.2.2.4). The purpose of the assay is to detect these HPV antibodies before and after vaccination with the 9vHPV vaccine.

For the 9-valent HPV cLIA, 9 HPV type-specific, yeast-derived virus-like particles (VLPs) are coupled to 9 distinct Luminex magnetic microspheres, one for each VLP type. Each VLP-coupled microsphere has its own distinct fluorescent dye that can be recognized by excitation with an infrared laser, allowing for the measurement of antibodies against multiple HPV types from a single test of an individual's serum. HPV type-specific monoclonal antibodies labelled with R-Phycoerythrin (R-PE) compete with an individual's serum antibodies for binding to the neutralizing epitopes of the VLPs. The fluorescent signal from the R-PE-labelled, type-specific monoclonal antibodies is inversely proportional to the anti-HPV antibody concentration of a sample.

The IgG LIA or total IgG assay is slightly more sensitive than the cLIA and has been previously used as a secondary assay for supportive analyses in several studies with qHPV vaccine to assess antibody persistence. The IgG LIA measures antibodies to the 9 HPV types covered by the 9-valent HPV vaccine (HPV 6, 11, 16, 18, 31, 33, 45, 52, and 58).

For the 9-valent HPV IgG LIA, HPV type-specific VLP-coupled microspheres are incubated with an individual's serum, washed to remove excess sera, and incubated with an R-PE-conjugated goat anti-human IgG antibody. The intensity of the fluorescent signal from the R-PE-labelled conjugate is proportional to the anti-HPV antibody concentration of a sample.

For the 9-valent HPV cLIA and IgG LIA, antibody concentrations are derived from a standard curve, which is generated using a reference standard made from a pool of serum from individuals immunized against the nine HPV types. A standard curve for each HPV type is calculated using a weighted 4 parameter logistic curve fit. Results are expressed as milliMerck Units/ml (mMU/mL).

For the 9-valent HPV cLIA and IgG LIA, serostatus cut-offs for each HPV type will be predefined. A study subject will be considered seropositive to a given HPV type at Visit 1 if her anti-HPV titre, as assessed by cLIA/ IgG LIA, is greater than or equal to the corresponding serostatus cut-off for that HPV type. A subject will be considered seronegative to a given HPV type at Visit 1 if her anti-HPV titre, as assessed by cLIA/ IgG LIA, is less than the corresponding serostatus cut-off for that HPV type.

#### **8.2.2.4 HPV16/18 virion detection and antibody titration (ELISA, electronic microscopy)**

Enzyme-linked immunosorbent assays (ELISA) will be performed as primary method to detect and quantify HPV16/18 antibodies in serum samples of RIFT-HPV Cohort 1 and RIFT-HPV Cohort 2, and HPV16/18 virions in cervical, anal, urine, vulvar and oral samples from the study subjects. The purpose of the test is to distinguish reduction of infectivity due to 9vHPV vaccination from non-productive HPV infections.

A sandwich ELISA assay will be used to detect the major capsid protein L1 of HPV 16/18 present in serum and in exudates of productive infections. Samples will be centrifuged for 20 minutes at 3000 rpm and supernatants recovered and added to microtiter plates with wells coated with anti-HPV 16/18 L1 capture antibodies. Samples and controls will be incubated for 20 minutes to let the antigens bind to the capture antibodies and afterwards a washing step will be done for removing unbound substances. A reporter antibody conjugated with HRP enzyme will be added for antigen detection and incubated for 1 hour, followed by a washing step to remove the excess of reporter antibody. Finally, a chromogenic HRP substrate will be added, and optical density measured for indirect quantification of bound virions.

Productive infections will be detected through the identification of new viral particles by electron microscopy (EM) in cervical samples and HPV positive oral and anal samples as previously described. EM experiments will be performed using the scientific platform of the University of Barcelona (UB). The EM will offer a direct measure of viral particles to confirm the virus production, while the ELISA test will offer a faster and more sensitive measurement especially in samples in which a low viral load is expected (oral samples).

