| Anal sample collection                                                                                                                         | ✓ | ✓ | ✓ | ✓ |
| First-void urine collection                                                                                                                    | ✓ | ✓ | ✓ | ✓ |
| Oral sample collection                                                                                                                         | ✓ | ✓ | ✓ | ✓ |
| Blood sample collection                                                                                                                        | ✓ | ✓ | ✓ | ✓ |
| Vaccination + 30 min monitoring for post-vaccination immediate adverse events                                                                  | ✓ | ✓ | ✓ |   |
| AE/SAE assessment                                                                                                                              |   | ✓ | ✓ | ✓ |
| Laboratory analytical procedures                                                                                                               |   |   |   |   |
| HPV infective capacity in-vitro evaluation (E1^E4-HaCaT model)                                                                                 | ✓ | ✓ | ✓ | ✓ |
| Anti-HPV 6/11/31/33/45/52/58 L1 ab detection/titration by cLIA in cervical, anal, oral, urine, vulvar and blood samples from RIFT/HPV 1 cohort | ✓ | ✓ | ✓ | ✓ |
| Anti-HPV 16/18 L1 ab detection/titration by ELISA in cervical, anal, oral, urine, vulvar and blood samples from RIFT/HPV 1 and 2 cohorts       | ✓ | ✓ | ✓ | ✓ |
| HPV test and genotyping (Anyplex HPV28) in cervical, anal, urine, vulvar and oral samples                                                      | ✓ | ✓ | ✓ | ✓ |

|                                                                                                            |   |   |   |   |
|------------------------------------------------------------------------------------------------------------|---|---|---|---|
| HPV16/18 virion detection (ELISA, electronic microscopy) in cervical, anal, urine, vulvar and oral samples | ✓ | ✓ | ✓ | ✓ |
|------------------------------------------------------------------------------------------------------------|---|---|---|---|

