#### **8.2.1.5 Blood Sample Collection**

A blood sample for serum anti-HPV antibody testing will be collected from study subjects on each of the four study visits. On Visits 1 to 3, blood sample will be collected before administration of the study vaccine's dose.

Blood will be extracted in a red-top vacutainer tube by standard venipuncture procedures, mixed by gently inverting the tube 5 times, left at room temperature for coagulation between 30 and 60 minutes, and centrifuge at 1500 g for 15 minutes to separate serum from coagulated blood. After centrifugation, serum (top layer) will be carefully collected with a pipette into a new tube and immediately placed in ice until stored at -80°C.

Serum samples will be shipped in dry ice to the designated laboratory for anti-HPV L1 antibody titration (cLIA).

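### The only ELISA written out in section 8.2.2.4 detects L1 antigen, not anti-L1 antibody, and the laboratory sections limit antibody assays to serum although the endpoints and analysis set need antibody in five mucosal fluids

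*Protocol*

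**What the plan says.** Section 8.2.2.4 opens by making ELISA the "primary method to detect and quantify HPV16/18 antibodies in serum samples of RIFT-HPV Cohort 1 and RIFT-HPV Cohort 2", and separately the method for virions in the mucosal samples. It then writes out one ELISA. This is a "sandwich ELISA assay will be used to detect the major capsid protein L1 of HPV 16/18 present in serum and in exudates", using "microtiter plates with wells coated with anti-HPV 16/18 L1 capture antibodies", a labelled reporter antibody to reveal the captured antigen, and an optical density read as the quantity of virions bound. Section 8.2.2.3 sends the reader to this section for the HPV16/18 antibody ELISA.

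Section 8.2.2.3 describes cLIA "in serum samples from study's subjects of RIFT-HPV Cohort 1". It describes IgG LIA on serum as well, without assigning it to a cohort. On positivity it says "For the 9-valent HPV cLIA and IgG LIA, serostatus cut-offs for each HPV type will be predefined"; nothing equivalent is said for ELISA.

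The schedule in section 1.2.2 lists, at all four visits, "Anti-HPV 16/18 L1 ab detection/titration by ELISA in cervical, anal, oral, urine, vulvar and blood samples from RIFT/HPV 1 and 2 cohorts". The endpoint tables (sections 1.1.5 and 3), the overall design (section 4.1) and the definition of antibody exudation (section 9.1.4) likewise assign ELISA or cLIA antibody detection to the mucosal fluids. Sections 8.2.1.1 to 8.2.1.4 collect each of those fluids partly for that purpose.

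**The concern.** An antibody endpoint needs an assay that binds antibody. Plates coated with anti-L1 antibody bind L1, so they report how much capsid is in the sample, not how much anti-L1 antibody the woman has made. Section 8.2.2.4 applies that format to serum, the matrix its own opening sentence assigns to antibody. A laboratory following the written steps would therefore measure the wrong analyte there.

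The antibody results matter in three places:

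- Mucosal antibody is listed under the primary objective, to tie any fall in infectivity to neutralising antibody.
- Section 9.1.1.1.2 removes post-vaccination cases that lack mucosal antibody or lack seroconversion, so these assays decide who enters the primary analysis.
- Section 9.1.1.2 plans a sensitivity analysis in women who are seronegative before vaccination, and the secondary objective reports seroconversion. Both need a serum antibody result with a cut-off.

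**Working it through.** The point is one of assay description and rests on no sample-size or power figure in the plan. The check is to set the sections side by side and then count the samples concerned.

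**1. What the ELISA is for, against what is described.** Stated purpose: HPV16/18 antibody in serum of both cohorts, and virions in mucosal samples (opening of 8.2.2.4). Described procedure: anti-L1 coating, L1 as target, virion readout, applied to serum and exudates. The procedure serves the second purpose only. The cross-reference from 8.2.2.3 ends at a method that does not measure antibody.

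**2. Which fluids the antibody assays cover.**

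| Assay | Laboratory section | Endpoints, schedule, design, definitions |
|---|---|---|
| cLIA | serum, RIFT-HPV 1 (8.2.2.3) | serum and five mucosal fluids, RIFT-HPV 1 (1.1.5, 1.2.2, 3, 4.1) |
| IgG LIA | serum, no cohort named (8.2.2.3) | not assigned |
| ELISA, antibody | serum, both cohorts; no antibody format given (8.2.2.4) | serum and five mucosal fluids, both cohorts (1.1.5, 1.2.2, 3, 4.1) |

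**3. Cut-offs and units.** Serostatus cut-offs are promised for cLIA and IgG LIA only. The only antibody unit in the protocol is the milliMerck unit per mL (8.2.2.3, 9.1.4), which 8.2.2.3 ties to those two assays. The antibody ELISA has no format, cut-off or unit.

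**4. cLIA type list.** Sections 1.1.5, 3, 4.1 and 8.2.2.3 give all nine vaccine types. The schedule row in 1.2.2 gives seven, without 16 and 18. If the schedule row were followed, HPV16/18 antibody in RIFT-HPV 1 would also rest on the ELISA.

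**5. Count at minimum enrolment** (39 and 30 women, four visits, five mucosal fluids):

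- RIFT-HPV 2 sera: 30 x 4 = 120.
- RIFT-HPV 2 mucosal samples: 30 x 4 x 5 = 600.
- RIFT-HPV 1 mucosal samples: 39 x 4 x 5 = 780. These are assigned to cLIA, so they belong to the scope conflict and not to the missing assay.

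**6. Illustration of the analysis-set dependence.** Section 9.2.2 plans the anal comparison on 28 women: 0.60 x 30 = 18 from RIFT-HPV 2 plus 10 from RIFT-HPV 1 (0.28 x 39 = 10.9, taken as 10). This reproduces the plan's 28. Suppose, as a worst case, that no RIFT-HPV 2 woman could be shown to meet the antibody criteria. Then 28 - 18 = 10 would remain. The protocol gives no standard deviation, so take the standardised paired effect implied by 80% power, two-sided 0.05 and n = 28:

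- Normal approximation: d = (1.960 + 0.842)/sqrt(28) = 0.53. Power at n = 10 is Phi(0.529 x sqrt(10) - 1.960) = Phi(-0.29) = 0.39.
- Noncentral t: d = 0.55, and power at n = 10 is 0.34.

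The planned test is the Wilcoxon signed rank, so these figures are only indicative.

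**The case against.** The strongest reply is that this is a gap in bench detail. Section 8.2.2.4 does name an antibody ELISA for both cohorts, and several sections assign ELISA or cLIA to the mucosal fluids. The collection sections already take those fluids for antibody detection, and a laboratory manual that is not shown may hold the method.

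Much of that stands, and it rules out stronger readings that a reader might infer:

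- **That the antibody endpoint cannot be obtained, or that RIFT-HPV 2 has no antibody measurement.** The documents do not support this. The assay is mandated; what is missing is a description that measures antibody.
- **That all 1,380 mucosal samples (600 + 780) lack an antibody assay.** The 780 from RIFT-HPV 1 are assigned to cLIA, whose mechanism is described.
- **That only serum can be sent for cLIA.** Section 8.2.1.5 mentions shipping serum because it is the blood-collection section. It excludes nothing else.
- **That the antibody and virion criteria become one signal and the antibody-infectivity association reverses.** This requires the laboratory to record antigen as antibody. Section 9.1.4 defines the two as separate variables and section 9.1.1.1.2 lists them as separate criteria.

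What the reply does not answer is that the protocol is not silent here. It writes out steps for an antigen assay and applies them to serum. It also words the antibody assays for serum against its own schedule. A numeric cut-off may be left to other documents; the analyte and the sample type may not be left in contradiction.

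**Conclusion.** The point holds as an error and an internal contradiction in the laboratory sections. The only ELISA procedure in 8.2.2.4 cannot measure anti-L1 antibody, although that section, 8.2.2.3 and the schedule rely on ELISA for HPV16/18 antibody. The serum-only wording of 8.2.2.3 and 8.2.2.4 contradicts the endpoints, the schedule and the analysis-set criteria.

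The exposure is greatest in RIFT-HPV 2, with 120 sera and 600 mucosal samples at minimum enrolment, because it has no cLIA to fall back on. In RIFT-HPV 1 the defect is limited to scope, provided that the nine-type cLIA list is the operative one. The fall in anal cases from 28 to 10 is a worst case that depends on RIFT-HPV 2 yielding no usable antibody result, and it is not a forecast. Because the antibody results gate entry to the primary analysis, the correction should be made before antibody testing is run.

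**What to change.** 1. In 8.2.2.4, restrict the L1-capture sandwich ELISA to virion detection in the mucosal samples and remove serum from its scope.
2. Set out a separate assay that detects anti-L1 antibody for HPV16 and HPV18. An indirect ELISA on VLP-coated wells, or the IgG LIA already described in 8.2.2.3, would both serve. State the matrices, the cohorts, a positivity cut-off per type and the units.
3. Extend the scope of 8.2.2.3 and 8.2.2.4 to the mucosal samples listed in the schedule. The collection sections already name antibody detection as a purpose and need no change on that point.
4. Reconcile the cLIA type list: seven types in the schedule, nine in sections 1.1.5, 3, 4.1 and 8.2.2.3.

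The cost is more than wording, since antibody assays described for serum would need set-up and cut-off definition in the mucosal fluids. No visit or sample is added, because the schedule already includes these measurements.

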## 8.3 STUDY SAFETY ASSESSMENTS

### 8.3.1 Physical Examination

A physical examination is optional and will be conducted by the Investigator/Subinvestigator as per institutional standard on Visit 1 to determine whether the candidate meets eligibility criteria for enrolment.

Height and weight will be recorded on Visit 1 before administration of study vaccine.

Physical examination details will be recorded in the subject's study chart. Any medical condition identified during physical examination will be documented in the data collection system. The Investigator will pay special attention to clinical signs related to previous serious illnesses.

### 8.3.2 Pregnancy test

A urine sample will be collected from candidates in Visits 1 to 4, to perform a pregnancy test by the study personnel. A positive result will exclude the candidate from participation in the study.

### 8.3.3 Temperature Measurements

The Investigator/Subinvestigator or nurse will assess the subject's temperature before study vaccine administered. It is administered on Day 1/ Visit 1, Month 2/ Visit 2, and Month 6/ Visit 3; and if the subject has fever (defined as temperature of  $\geq 37.8^{\circ}\text{C}$ ) within the 24-hour period prior to receiving a study vaccination, she should not receive the study vaccine. The vaccination visit should be rescheduled until after the fever has resolved.

In the 15 days following post vaccination, if a temperature measure indicates a fever (defined as  $\geq 37.8^{\circ}\text{C}$ ), an AE of "fever" must be documented in the subject's study chart.

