### 1.2.2 Schedule of Activities (SoA)

|                                             | Day 1   | Month 2
(±3 weeks) | Month 6
(±4 weeks) | Month 7
(-3 weeks/
+7 weeks
from Visit 3) |
|---------------------------------------------|---------|-----------------------|-----------------------|----------------------------------------------------|
|                                             | Visit 1 | Visit 2               | Visit 3               | Visit 4                                            |
| Sign Informed Consent                       | ✓       |                       |                       |                                                    |
| Review eligibility criteria                 | ✓       |                       |                       |                                                    |
| Urine sample and pregnancy test performance | ✓       | ✓                     | ✓                     | ✓                                                  |
| Temperature (fever ≥ 37.8°C)                | ✓       | ✓                     | ✓                     | ✓                                                  |
| Questionnaire                               | ✓       | ✓                     | ✓                     | ✓                                                  |
| Height and weight measurement               | ✓       |                       |                       |                                                    |

|                                                                                                                                                |   |   |   |   |
|------------------------------------------------------------------------------------------------------------------------------------------------|---|---|---|---|
| Medical history, past and current medication and vaccination                                                                                   | ✓ | ✓ | ✓ | ✓ |
| Gynecological examination in routine visit                                                                                                     | ✓ | ✓ | ✓ | ✓ |
| Cervical sample collection                                                                                                                     | ✓ | ✓ | ✓ | ✓ |
| Vulvar sample collection                                                                                                                       | ✓ | ✓ | ✓ | ✓ |

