Study subjects will be followed thorough the whole duration of the study for possible injection-site AEs, systemic AEs, SAEs and deaths regardless of causality. All AEs and SAEs will be recorded by the study Investigator at each study visit (section 8.4).

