### 8.4.3 Detection and Recording of Adverse Events

All AEs will be reported by the study subject to the Investigator at each study visit by open-ended, nonleading verbal questioning, and will be recorded based on subject's reporting, careful clinical observation of the subject and results of laboratory tests.

All AEs (serious or not) occurring during the study will be noted in the subject's medical history and recorded in the study CRF. The Investigator will also note whether the adverse event is, based on his/her judgment, related or not to the study vaccine. This decision should also be noted in the medical history and CRF.

At each visit, all AEs experienced by the patient since the previous visit should be recorded in the specific adverse event form of the CRF.

The following will be recorded for each event:

- description, severity (grade 1, 2, 3, 4 and 5),
- duration (start and end dates),
- causal relationship with the study vaccine (according to the above attributability criteria) for which this causal relationship is suspected,
- treatment (if applicable) or actions taken,
- possible alternative explanations,
- predisposing factors,
- outcome,
- for a pre-existing AE that has worsened in terms of severity or frequency, the meaning of the change should be specified.

AE's severity degree provides a qualitative assessment of the extent or intensity of an adverse event elicited by the Investigator or reported by the subject. Severity does not reflect the clinical seriousness of the event, only the grade or extent of the complaint or incidence.

The severity of an AE will be rated based on the Division of AIDS Adverse Event Grading Table.

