#### 8.4.6 Expedited Reporting of SUSARs by the Sponsor

It is the responsibility of the Sponsor/ representative to communicate any SUSAR occurring from the time of subject's inclusion in the study through the complete duration of the study (7 months) to the regulatory authorities, i.e., the Spanish Agency of Medicines and Sanitary Products (AEMPS) through EudraVigilance, and to the competent bodies of the Autonomous Communities in whose territory the study is being conducted.

According to AEMPS regulations (section 8 of the AEMPS' Instructions for the Conduction of Clinical Trials), it is not necessary for the Sponsor to communicate study SUSARs to the EC.

As defined in section 8.4.1, a SUSAR is any adverse event meeting the following three criteria:

- Serious,

- Unexpected
- Associated to the administration of the study vaccine.

The study Sponsor will report the adverse experience to MSD, the study funder, as specified in the study agreement signed with MSD.

The latest deadline for SUSARs reporting will be 15 calendar days from the time the Sponsor becomes aware of the event. For SUSARs causing death or being life-threatening for the subject, the latest deadline will be 7 calendar days. When possible, complete information on the event will be provided in the following 8 days.

Information on adverse events that are not serious or unexpected and on those considered unrelated to the study vaccine will be collected in tabular form at the end of the study.

The Sponsor/representative will keep a record of all AEs reported by Investigators. These records will be submitted to the Spanish Regulatory Agency when requested.

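### Fever is to be recorded from a temperature in the 15 days after each dose, but none is scheduled there after doses 1 and 2, so fever is likely to be undercounted, and unevenly by dose

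*Protocol*

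**What the plan says.** Section 8.3.3 contains two rules. For the vaccination visits, the investigator, subinvestigator or nurse "will assess the subject's temperature before study vaccine administered". For the period afterwards, the trigger for a fever event is: "In the 15 days following post vaccination, if a temperature measure indicates a fever", with the threshold at 37.8°C or above. The rule does not say who takes that reading or when.

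The Schedule of Activities (1.2.2) has one temperature row, "Temperature (fever ≥ 37.8°C"), ticked at Visits 1, 2, 3 and 4. The visit windows there are "Month 2 (±3 weeks"), "Month 6 (±4 weeks"), and Month 7 with minus 3 to plus 7 weeks relative to Visit 3. Doses are given at Visits 1 to 3.

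Section 4.1 describes the safety follow-up: "Study subjects will be followed thorough the whole duration of the study for possible injection-site AEs, systemic AEs, SAEs and deaths regardless of causality". Section 8.4.3 gives the method: "All AEs will be reported by the study subject to the Investigator at each study visit by open-ended, nonleading verbal questioning", covering events since the previous visit. Section 8.4.6 says that events which are not serious, not unexpected or not related "will be collected in tabular form at the end of the study".

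**The concern.** A mandatory recording rule has a 15-day window, and the schedule supplies no reading within it for two of the three doses. What remains is a reading that the woman takes herself, although nothing in the protocol text shown asks her to take one, and then mentions at a later visit when asked a non-leading question. Injection-site reactions, which section 4.1 says are followed, depend on the same recall once the 30-minute observation is over.

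At stake is the reading of the end-of-study adverse event table. Without a stated method, a reader cannot tell a dose after which no fever occurred from one after which nobody measured. Section 5.1 expressly admits women with HIV, transplant immunosuppression or autoimmune disease, so tolerability in this population is of some interest, although safety is not an objective of the study.

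**Working it through.** The protocol states no figure to reproduce here: it gives no fever rate and no sample size for safety. The check is calendar arithmetic.

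**Inputs.** Visit 2 at 2 months ± 21 days and Visit 3 at 6 months ± 28 days, both from dose 1. Visit 4 is read as one month after Visit 3 with a tolerance of −21 to +49 days (an assumption about how that window is meant). A month of *m* days is varied from 28 to 30.4375 (assumption).

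**Formulas for the days from a dose to the next scheduled temperature.**
- Dose 1 to Visit 2: from 2m − 21 to 2m + 21.
- Dose 2 to Visit 3: earliest (6m − 28) − (2m + 21) = 4m − 49; latest (6m + 28) − (2m − 21) = 4m + 49.
- Dose 3 to Visit 4: from m − 21 to m + 49.

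| Month length (days) | Dose 1 to Visit 2 | Dose 2 to Visit 3 | Dose 3 to Visit 4 |
|---|---|---|---|
| 28 | 35 to 77 | 63 to 161 | 7 to 77 |
| 30 | 39 to 81 | 71 to 169 | 9 to 79 |
| 30.4375 | 39.9 to 81.9 | 72.8 to 170.8 | 9.4 to 79.4 |

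**Comparison with day 15.** After doses 1 and 2 the earliest possible readings are day 35 and day 63, so none can fall in the window under any month length. After dose 3 a reading falls in the window only if Visit 4 comes at least m − 15 days early, which is 13 to about 15 days. With a 30-day month that is days 9 to 15, or 7 of the 71 allowed days.

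**Share of doses.** At the minimum enrolment, 39 + 30 = 69 women and 69 × 3 = 207 planned doses. Doses 1 and 2 make up 69 × 2 = 138 of them, two thirds.

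**Length of recall, counted from the fever.** For a fever on day 15, the shortest interval is 35 − 15 = 20 days after dose 1 and 63 − 15 = 48 days after dose 2. For a fever soon after the dose, the longest is about 82 and 171 days. The nominal gaps from dose to next visit are two, four and one months for doses 1, 2 and 3, so recall is shortest after dose 3, the only dose that can also have a scheduled reading.

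**Illustration of size.** With an assumed true fever rate of 2%, 5% or 10% per dose, 69 women would have 1.38, 3.45 or 6.9 fevers per dose. The number recorded could be anything from none to all of these, depending on a capture rate that the documents do not give.

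**The case against.** The strongest reply is that section 8.3.3 is conditional and is not limited to study readings. A woman's own thermometer reading triggers it, and section 8.4.3 requires every event since the previous visit to be recorded. Section 8.1.5 adds a prompt tied to each dose: other medications are documented from 3 days before to 14 days after each vaccination, which could bring up treatment taken for a fever. The participant information sheet is a separate document and might ask women to take their temperature at home. Open, non-leading questioning is also a deliberate and accepted method.

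Most of this stands. A reader might infer that the table will show fever as absent or far too rare, or that a result of 0 in 207 doses would give a falsely reassuring one-sided upper 95% limit of 1 − 0.05^(1/207) = 1.4% per dose. The documents support neither inference. Self-reported fever has a route into the record, no capture rate is given, and the protocol plans no per-dose fever rate with a confidence limit.

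The mismatch itself is untouched. The medication review reaches only women who took something and remember it, and the protocol text names no diary, home reading or interim contact. The telephone call in section 4.4 appears only in the definition of study end.

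**Conclusion.** The point holds as a minor one. No scheduled temperature can fall in the 15-day window after 138 of the 207 planned doses, and after the other 69 only with an early Visit 4. Fever is therefore likely to be undercounted, and ascertainment differs by dose, so a comparison of fever across doses would partly reflect how and when women were asked. The scheduling result rests on the stated windows and does not depend on month length; the dose 3 result also rests on the tolerance reading of the Visit 4 window. The direction of the bias is a judgement about unprompted recall, and its size cannot be derived from the documents. Fever is not an objective or endpoint, so the infectivity and antibody conclusions are unaffected.

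**What to change.** Reconcile sections 8.3.3 and 8.4.3 with the Schedule of Activities:

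- In 8.3.3, state that fever in the 15 days after a dose is self-measured and reported by the woman at her next visit.
- At the adverse event assessments already scheduled at Visits 2, 3 and 4, ask every woman one fixed closed question: any measured temperature at or above the protocol's own fever threshold, or any injection-site reaction, in the 15 days after the previous dose, and on what date.
- Record the answer on the adverse event form, and keep open-ended questioning for all other events.
- Tabulate these events by dose, labelled as recalled, with the number of women asked as the denominator.

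The cost is one question at existing visits and one table. Recall error remains, and recorded rates will be higher than under open questioning, so they should not be set beside rates collected by open questioning without saying so.
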